##### Gating Strategy

Cells will be gated for size, shape, and granularity using forward and side scatter parameters, as previously described by our group [78,79]. Briefly, serial gating steps will be applied to quantitate cellular populations. First, dead cells will be excluded, and then, a region will be set to encompass lymphocyte-, monocyte-, and granulocyte-enriched areas, followed by doublet discrimination, T cell (CD3) and B cell (CD19) elimination. For COP cells, after gating on live single mononuclear cells (on forward and side scatter plots), the CD45 and osteocalcin double positive cells will be calculated. Cutoff points to assign antigen positivity will be performed against matching FMO controls. The use of FMO significantly increases the sensitivity and specificity of analysis, as they effectively minimize the effect of nonspecific antibody binding and cell-specific autofluorescence. The gating quantification will be performed twice for the accurate quantification of the percentage of COP cells.

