### Objectives

The primary objective of this study is to determine the change in circulating ucOC following acute exercise interventions between older adults with low and high muscle function (stratified based on leg muscle quality [LMQ]; see the *Lower Limb Maximal Strength and LMQ* section for the LMQ equation). To extend the current knowledge of ucOC in humans, and as an adjunct to this study, we will also perform in vitro experiments on cultured primary myotubes to uncover the mechanistic pathways of action of ucOC. In addition, as a secondary objective, we will aim to quantify the lineage of COP cells before and after exercise, as COP cells can potentially act as a regeneration and antiaging inducible factor and a precursor for osteocalcin.

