##### Quantification of COP Cells

COP cell analysis will be performed as described previously [78,79]. In brief, peripheral blood samples (20 mL) will be collected (EDTA tubes) and processed for Ficoll-based gradient separation, and approximately 5×10^6^ peripheral blood mononuclear cells (PBMCs) will be obtained. Approximately 1×10^6^ PBMCs will be resuspended in fluorescence activated cell sorting (FACS) buffer, followed by a 10-minute blocking with fragment crystallizable receptor blocking reagent (BD Biosciences). Staining will then be performed with a viability marker (30 minutes), followed by washing (×2) with phosphate buffered saline (containing 5% fetal calf serum). Cells will be incubated with mouse antihuman CD45-Pacific Blue, CD3-PerCP, and CD19-APC (40 minutes). Staining of intracellular components will be permeabilized with Cytofix/Cytoperm (BD Biosciences) according to the manufacturer’s instructions, followed by incubation with mouse antihuman osteocalcin-phycoerytrhin at 4 °C (40 minutes), and then washed with Perm or wash buffer (×2).

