##### Flow Cytometry

Cells will be analyzed using a BD FACS Canto II. FACS DiVa software will be used to analyze 50,000 total events for each sample and for the fluorescence minus one (FMO) controls. A total of 3 lasers and 8 different photomultiplier tube (PMT) channels will be used for the 6-color staining panel. Two FMOs will contain fluorochromes, except for the one to be controlled for. Compensation beads will be used to set the compensation controls for each fluorochrome. The PMT voltage values for fluorochromes will be set for each cell type based on the compensation controls. Doublet discrimination will be applied, and viability will be assessed by negative staining using the Live/Dead stain. Offline analysis will be performed using Flow Jo analytical software (Treestar).

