## Discussion

Previous research suggests that crosstalk exists between the skeleton and skeletal muscle; however, this crosstalk has not been fully described or clearly elucidated, particularly in humans. In addition, a lack of physical activity accelerates the widespread cellular and molecular changes induced by aging, resulting in an increased prevalence of many chronic diseases [94]. Detecting the age-related conditions associated with inactivity and early intervention are essential for reducing the economic burden of aging on the health care systems worldwide. The development of affordable and universally accessible ways to prevent chronic disorders, such as tailored exercise programs, in combination with the development of robust blood biomarkers, will considerably improve the ability to predict and detect chronic diseases and reduce the health and economic burden caused by aging in a cost-effective manner [95].

This project is designed to uncover a novel crosstalk pathway between bone and muscle in older adults via ucOC. Current evidence from predominately cross-sectional studies suggests that osteocalcin, via ucOC, in humans may be associated with muscle function [10,19]. Evidence from animal and preclinical studies is encouraging, indicating a promising role for ucOC in improving muscle metabolism and function [16,17,25]. However, the roles of ucOC in humans and its relationship with muscle function and metabolism remain unknown. Evidence suggests that COP cells have a dynamic capacity to mobilize to sites of fracture repair and have the capacity to be upregulated under varying pathological or physiological bone forming processes, such as puberty and fracture [79,96-102]. However, it is unknown whether exercise stimulus, with osteogenic capacity, can increase the COP cell population and upregulate tOC and therefore ucOC.

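### COP cells are read out only as a percentage of gated cells, which cannot separate a change in COP cells from an exercise-induced change in the other cells of the denominator

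*Protocol article*

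**What the plan says.** Objectives introduces COP cells in these words: "as a secondary objective, we will aim to quantify the lineage of COP cells before and after exercise". Biospecimen Sampling Protocols lists COP among the measures followed at 0, 30, 60 and 120 minutes after each session. The Discussion states the open question: "it is unknown whether exercise stimulus, with osteogenic capacity, can increase the COP cell population and upregulate tOC and therefore ucOC". COP cells appear under neither Primary Outcomes nor Secondary Outcomes.

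For the measurement, Quantification of COP Cells says "peripheral blood samples (20 mL) will be collected (EDTA tubes) and processed for Ficoll-based gradient separation", and then "Approximately 1×10^6^ PBMCs will be resuspended in fluorescence activated cell sorting (FACS) buffer". Under Flow Cytometry, "FACS DiVa software will be used to analyze 50,000 total events for each sample". Gating Strategy describes serial steps, "followed by doublet discrimination, T cell (CD3) and B cell (CD19) elimination". For COP cells it adds: "after gating on live single mononuclear cells (on forward and side scatter plots), the CD45 and osteocalcin double positive cells will be calculated". It closes with "The gating quantification will be performed twice for the accurate quantification of the percentage of COP cells".

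None of these sections describes a blood count, counting beads or a conversion to cells per volume. The screening blood tests (Quantification of Bone Remodeling and Cardiometabolic Biomarkers) name no blood count either, although that list ends with an open category.

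**The concern.** The question in the Discussion is about amount: does exercise put more COP cells into the circulation, and could they in turn raise total and undercarboxylated osteocalcin? The readout is a share. A share follows the number only while its denominator is stable. If a bout of exercise changes the other gated cells within the 0 to 120 minute window and supine rest does not, the share moves although no COP cell has been added or lost, or it stays still although COP cells have risen.

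Such a shift would follow condition and time point, so it would look like an exercise effect or cancel one. If the low and high muscle function groups differed in their white-cell response, it could also look like a group difference. At stake is the interpretation of the COP objective. The primary ucOC outcome is not affected.

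**Working it through.** **Inputs from the article:** percentage readout; about 1×10^6 cells stained; 50,000 events per sample; T and B cells eliminated during serial gating; control session of 30 minutes' supine rest. **Assumed, because the article gives neither:** the baseline COP share and the exercise response of the other cells. The article gives no COP figure, so there is nothing to reproduce.

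**1. Basic relation.** Let the COP number per mL change by a factor m and the denominator by a factor k. The percentage changes by m/k − 1; with COP constant (m = 1), by 1/k − 1.
- k = 0.8: 1/0.8 − 1 = +25.0%
- k = 1.2: 1/1.2 − 1 = −16.7%
- k = 1.5: 1/1.5 − 1 = −33.3%

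**2. COP cells counted inside the denominator.** If only the other cells change by k and the baseline share is p, the new share is p/(p + (1 − p)k). With p = 1%:
- k = 0.8: 0.01/(0.01 + 0.792) = 1.247%, or +24.7%
- k = 1.5: 0.01/(0.01 + 1.485) = 0.669%, or −33.1%

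For p from 0.5% to 5% the results run from +24.8% to +23.5% (k = 0.8) and from −33.2% to −32.2% (k = 1.5). The baseline share hardly matters.

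**3. Masking.** With p = 1%, COP ×1.5 and other cells ×1.5 give 1.000%: a real rise reads as no change. COP ×1.2 and other cells ×1.5 give 0.012/(0.012 + 1.485) = 0.802%, an apparent fall of about 20%.

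**4. Which denominator.** The article does not name it. Take an assumed mix of 60 T, 10 B, 10 NK, 19 monocytes and 1 COP cell per 100. The share is 1/100 = 1.000% over all mononuclear cells and 1/30 = 3.333% once T and B cells are removed.

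| Assumed shift, COP constant | Over all mononuclear cells | Over CD3−/CD19− cells |
|---|---|---|
| T and B ×1.5 | 1/135 = 0.741% (−25.9%) | 1/30 = 3.333% (0%) |
| NK ×3 | 1/120 = 0.833% (−16.7%) | 1/50 = 2.000% (−40.0%) |

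Removing T and B cells protects against shifts in those cells and makes the score more sensitive to the cells that remain.

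**5. Safeguards in the plan.** Gating the same events twice improves repeatability and leaves the denominator as it was. Comparison with the rest session removes what all sessions share, such as time of day and repeated sampling. A shift present only after exercise remains.

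**6. Absolute count.** The percentage times the concentration of the same parent population is (C/D) × D = C. Apparent change is then 0% for every k when COP is constant, and m − 1 when COP changes. This needs stable blood volume and constant recovery. If blood volume changes by a factor v, all cell concentrations change by 1/v. If the count comes from recovered cells and recovery moves from r0 to r1, the result is off by r1/r0. The percentage cancels both, provided recovery is the same across cell types.

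**The case against.** The strongest reply has four parts.

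- **Condensed method.** The article summarises a cited laboratory method. The denominator, or even a conversion to cells per mL, may stand in the full protocol or in that method. This stands in part: one cannot conclude that no count is recorded. But the article does state its readout, and that readout is a percentage.
- **No leukocyte response in the documents.** Every k above is assumed, in size and in direction. This stands in full. The arithmetic shows what the readout cannot distinguish, not what will happen. A reader might infer that the COP result will be biased or have the wrong sign; nothing in the article supports that.
- **A relative frequency is a legitimate quantity, and the listed outcomes do not include COP.** Both are true, and both limit the weight of the point. The mismatch arises only when a percentage is used to answer the Discussion's question about the size of the population.
- **Cells per mL is imperfect too.** It responds to plasma-volume change, which may also follow exercise, and to error in cell recovery. It would also rise with a general mobilisation of mononuclear cells that is not specific to COP cells. This stands. A reader might infer that concentration should replace the percentage. The case supports reporting both.

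**Conclusion.** The point holds as a limit of the stated readout. The percentage cannot separate a change in COP cells from an exercise-induced change in the rest of its denominator: NK cells, monocytes and other CD3−/CD19− cells if T and B cells are removed first, and all mononuclear cells otherwise. The rest session does not control for this. With the COP number constant, a denominator ratio of 0.8 to 1.5 gives an apparent change of +25% to −33%. That range is an assumption chosen to show scale.

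A reader might set these percentages against the roughly 9% ucOC response quoted in the sample size section. That figure belongs to a different analyte and is no yardstick for COP cells. Because COP is a secondary objective outside the listed outcomes, this is an inexpensive improvement to the readout and its interpretation, not a flaw in the trial's main comparison.

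**What to change.** In Gating Strategy:

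1. Name the denominator of the COP percentage.
2. Report COP cells per mL alongside it, calculated as the percentage times the concentration of that same parent population. Use a count on the EDTA blood already drawn, or the mononuclear cell count where the actual number was recorded (the article gives only an approximate yield). If the denominator excludes T and B cells, first multiply the mononuclear count by the CD3−/CD19− share from the same gating.
3. If haemoglobin and haematocrit come with the count, correct for plasma-volume change.
4. State that an increase in the COP population will be claimed only if the absolute count supports it. Where only percentages exist, for example in samples already processed without a recorded count, describe the result as a change in relative frequency.

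**Cost:** a few sentences and a routine count per sample, with no extra draw or participant procedure. **Downsides:** recovery error and plasma-volume sensitivity in the concentration, and possibly incomplete data. By May 26, 2019, 38 of 54 participants (38/54 = 70%) had completed, so unless counts were kept, absolute values could be added only for the remaining 16.

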#### Muscle Sampling Protocol and Analyses

##### Summary of Sampling Procedure

If elected, the muscle samples (1 or 4) will be taken from the vastus lateralis (approximately 150 mg) under local anesthesia (xylocaine 1%) by percutaneous needle biopsy technique, modified to include suction [80]. Excised tissue will be snap frozen in liquid nitrogen and stored at −80° C for later analysis. Proteins involved in muscle degradation and hypertrophy (ie, anabolic and catabolic pathways; ubiquitin-proteasome, autophagy-lysosome, and caspase-3–mediated proteolytic pathways) as well as glucose uptake will be assessed, as described previously [81-84].

##### Protein Extraction and Western Blotting

All muscle samples (baseline and postintervention samples) will be used to analyze the content and activation of signaling proteins involved in muscle degradation and hypertrophy by using western blotting, as described previously [84-86]. Western blotting is a method commonly used to detect and analyze the abundance and posttranslational modifications (such as phosphorylation) of proteins. Briefly, muscle samples will be homogenized in a radioimmunoprecipitation assay buffer using a TissueLyzer (QIAGEN). Then, proteins in the lysate will be separated based on protein molecular weight via gel electrophoresis. Proteins will be subsequently transferred to a polyvinylidene fluoride membrane where specific proteins can be probed using specific antibodies. Finally, signals generated through electrogenerated chemiluminescence will be detected and analyzed using ChemiDoc Imaging Systems (Bio-Rad Laboratories).

##### Primary Skeletal Muscle Cell Culture

A portion of the muscle obtained at rest (baseline) will be used for cell culture for future molecular analyses [87]. This will be established according to the method described by Blau and Webster [88] and by Gaster et al [89] and previously detailed by McAinch et al [90]. Briefly, muscle samples (50-100 mg) will be washed, minced, and enzymatically dissociated with trypsin. Cells will be cultured in a coated flask with extracellular matrix, and the growth medium (α-minimal essential medium [α-MEM]+10% fetal bovine serum+0.5% penicillin-streptomycin+0.5% antifungal) will be changed every other day until they reach 80% confluence. Then, satellite cells will be selected using CD56+ magnetic microbeads (Miltenyi Biotec) and transferred to bigger flasks coated with extracellular matrix to increase cell number (up to 4 passages). Once the cells reach 80% confluence, they will be differentiated using a differentiation medium (α-MEM+2% horse serum+0.5% penicillin-streptomycin+0.5% antifungal) for 5-6 days. Before the experimental treatment, cells will be starved for 1 hour in a serum-free medium (α-MEM+0.5% penicillin-streptomycin+0.5% antifungal).

In vitro treatment with ucOC at concentrations of 0 ng/mL, 30 ng/mL, and 100 ng/mL in serum-free medium for 60 minutes and 24 hours in the presence or absence of insulin (100 nM for the last 15 minutes) for the determination of glucose uptake (2-deoxy-D-[3H] glucose) and western blotting will be performed. Analysis of targeted proteins (described above) will be performed as described previously [39,91]. The dose response is important because the physiological effect of ucOC in muscles from mice and humans may be different, and the concentrations used are all physiologically relevant.

#### Participant Retention and Withdrawal

Once a participant is enrolled into the trial, the study coordinator will keep in contact with him or her for the entire study period. We estimate that the dropout rate in this population will be approximately 10%. Participants may withdraw from the study at any given time. The investigators or medical staff may also withdraw participants from the study due to safety or medical concerns.

#### Statistical Analysis and Determination of Sample Size

The primary endpoint for this study is the change in ucOC levels from baseline to the peak, postintervention sampling time point. The analysis will include a comparison of changes in ucOC levels in response to each intervention from baseline to postintervention sampling time points (0, 30, 60, and 120 minutes) between the low muscle function and normal or high muscle function groups, by using repeated measures analysis of variance (ANOVA). Comparisons of multiple means will be examined using a 2-factor (exercise type×time point) repeated measures ANOVA. For all significant interaction and main effects, a priori comparisons of means (baseline vs all postexercise time points) will be conducted using the Fisher least significant difference test (*P<*.05). Multivariable regression models will be used to determine associations between selected measurements, adjusting for BMI and sex. Data will be analyzed using the Statistical Package for the Social Sciences, version 22 (SPSS Inc), and statistical significance will be declared at *P*<.05.

In 10 postmenopausal women, we previously reported that the change in ucOC levels following exercise is approximately 9% [39]. We will recruit 54 participants (equal number of men and women) who will be dichotomized as low muscle function versus high muscle function (27 per group). After adjusting for a loss to follow-up rate of 10% (5.4/54), this sample size will be large enough to detect an estimated 4% difference in changes in ucOC levels (SD 6%) between groups with a type I error rate of 5%, type II error rate of 20%, and power of >80% (G*Power 3.1.9.2 for Windows) [92].

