#### Randomization

Following baseline assessments, participants will be randomized into the acute intervention to explore the characteristics of older adults (by sex) with low or high muscle function (Figure 1). Participants will be randomized individually by a researcher external to this project (they will have no contact with the participants before or during the trial). This person will also have no intellectual or personal investment in the study design, data collection, or outcome. The order of the 3 conditions for each participant (AER, RE, or control) will be randomized using a sealed envelope method (block allocation) to prevent carryover effects between conditions. The envelopes will be stored separately in a locked cabinet, and each envelope will contain 3 pieces of paper that will state “AER,” “RE,” and “CON.” These pieces of paper will be folded to reduce their transparency.

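### The three-period crossover is analysed without a period term although all changes are taken from one first-visit baseline, and the text on order randomisation needs correcting

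*Protocol article*

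**What the plan says.** All places are in the Protocol article.

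- *Statistical Analysis and Determination of Sample Size*: changes in ucOC after each intervention are compared between the low and the normal or high muscle function groups "by using repeated measures analysis of variance (ANOVA"). The next sentence gives the only list of factors: "Comparisons of multiple means will be examined using a 2-factor (exercise type×time point) repeated measures ANOVA". Neither sentence names period, visit or sequence.
- *Biospecimen Sampling Protocols*: the resting sample is drawn at the first of the three intervention visits and serves all three. Each visit then has four post-intervention samples.
- *Acute Intervention*: visits are about 7 days apart, and that spacing is given as the washout.
- *Randomization*: the order of the conditions "will be randomized using a sealed envelope method (block allocation) to prevent carryover effects between conditions". On the mechanics, "each envelope will contain 3 pieces of paper that will state" the three condition labels, one per slip.
- The sample size is said to be enough to "detect an estimated 4% difference in changes in ucOC levels (SD 6%) between groups" with more than 80% power after 10% loss.

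**The concern.** In a three-period crossover, visit number is a design factor. Participants become used to the procedures, and a biomarker can drift over weeks. A model with exercise type and time point only has nowhere to put such an effect, so it goes into the error term or into whichever condition happened to fall later more often.

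The single baseline makes this more likely to matter here. The session that comes first is measured against a same-day baseline. The second and third are measured against samples about 7 and 14 days old. Any shift in resting ucOC over that time therefore enters the change scores of sessions 2 and 3 but not those of session 1.

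The Randomization section adds two difficulties. It gives prevention of carryover as the purpose of randomising order, which randomisation cannot achieve: random order spreads period effects over the conditions, while carryover is limited by the spacing of visits. It also uses the term block allocation for a procedure whose described mechanics, three slips in one envelope, settle one person's order and do not by themselves balance the six orders across people or within muscle-function groups.

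**Working it through.** **Inputs from the article.** Difference 4 percentage points, SD 6, alpha 5%, 54 recruited as 27 per group, 10% loss (54 × 0.9 = 48.6, taken as 24 per group), visits about 7 days apart, one baseline.

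**Assumptions.** Two-sided test, because sidedness is not stated. The SD of 6 excludes period drift. Drift is linear at G points per visit, so it adds 0, G or 2G to the change in sessions 1, 2 and 3. Drift sizes are illustrative, since the article gives none.

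**Step 1: the article's own figure.** Standard error of the group difference = 6 × √(2/24) = 1.73. Non-centrality = 4/1.73 = 2.31 on 46 degrees of freedom. Two-sided t power = 61.8% (one-sided 73.6%). The stated power above 80% is not reproduced. A repeated measures between-group calculation with 4 measurements and correlation 0.5 gives 81.6% with 48 participants, but the article states neither of those inputs, and that calculation tests a mean over time points, not a single peak change. This shortfall is a separate matter. It is shown only because 62%, not 80%, is the starting point below.

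**Step 2: drift left in the error term.** Under random order, a given condition falls in session 1, 2 or 3 with probability 1/3 each. The values 0, G, 2G have variance 2G²/3, so the SD within a condition becomes √(36 + 2G²/3).

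**Step 3: chance imbalance if orders are unrestricted.** SD of the drift part of the group difference within one condition = √(2/24 × 2G²/3) = 0.236G. For a contrast between two conditions over 48 people, the session positions differ by 1 in four of the six orders and by 2 in the other two. The mean square is (4×1 + 2×4)/6 = 2, and the SD is G√(2/48) = 0.204G. Simulation agreed with both.

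| Drift G per visit | SD with drift | Power, low vs high | Chance SD, group difference | Chance SD, condition contrast |
|---|---|---|---|---|
| 0 | 6.00 | 62% | 0 | 0 |
| 1 | 6.06 | 61% | 0.24 | 0.20 |
| 2 | 6.22 | 59% | 0.47 | 0.41 |
| 4 | 6.83 | 51% | 0.94 | 0.82 |

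The last two columns are in percentage points, against a standard error of 1.73 for the group difference. They become zero when the six orders are balanced within each group. The chance imbalance is part of the inflated SD, so steps 2 and 3 are not to be added together.

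**Step 4: missed samples, a side benefit of the fix.** The per-intervention group comparison uses 5 samples per participant (1 baseline + 4 post). If 1%, 2% or 3% of samples were missed independently (assumed) and incomplete participants were dropped, the loss would be 1 − 0.99⁵ = 4.9%, 1 − 0.98⁵ = 9.6% or 1 − 0.97⁵ = 14.1%. Power would go from 62% to 60%, 58% or 56%.

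**The case against.** Several stronger readings are tempting, and the article does not support them.

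- *That leaving out period biases the results systematically.* With order randomised it does not. A 4-point first-visit shift with an 11-versus-6 split of first sessions among 24 people would move a contrast by 4 × 5/24 = 0.83 points. But both the shift and the split are assumed, and that contrast is between conditions within one group. The low-versus-high comparison is touched only through added variance and through order differing between groups by chance.
- *That the orders are shown to be unbalanced.* The section does say block allocation, and an article can leave block size and the sequence list to the full protocol. Were order wholly unrestricted in a group of 24, there would be a 52% chance that first-session counts of the three conditions differ by 5 or more, and a 40% chance that some order occurs at most once. Those figures are conditional on a reading that the word block speaks against. What stands is that label and mechanics do not fit together.
- *That the plan prescribes complete-case analysis, with losses over all 13 samples* (1 + 3 × 4; 12%, 23% or 33% at the three missing rates above). The article states no missing-data rule, and a plan not shown may hold one. Dropping incomplete participants is only the usual behaviour of the named method. The 13-sample count fits the exercise type by time point analysis, which names no group factor, and a peak change can often still be found when one post sample is missing.

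It is also fair to say that the loss is small when drift is small, and that 38 of the planned 54 participants had completed by May 26, 2019, so a new order list can help only those not yet allocated.

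**Conclusion.** The point holds in a limited form. The article names the factors of its crossover model, and period is not among them, while its single-baseline design gives drift a direct route into the changes of sessions 2 and 3. The cost to the low-versus-high comparison is about 1 to 3 points of power for drifts of 1 to 2 points per visit, and about 11 points (62% to 51%) for a drift of 4. These sizes rest on assumed linear drift, on an SD of 6 that excludes it, and on a two-sided test with 24 per group. Most of the gap between these figures and the stated 80% is not due to the missing period term and should not be charged to it. The statement that randomising order prevents carryover is wrong as written. The allocation text is unclear, but imbalance is not shown.

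**What to change.** 1. **Analysis.** Replace the repeated measures ANOVA for ucOC with a linear mixed model in the same software. Fixed effects: period, condition, time point, muscle-function group and the relevant interactions among condition, time and group. Random effects: participant, and session within participant. Period costs two degrees of freedom. It removes the average drift between visits, though not each person's own day-to-day variation around the single baseline. The model also keeps participants with an occasional missed sample.
2. **Randomization wording.** Say that random order spreads period effects over the conditions, and that carryover is addressed by the spacing between visits that the article already describes as washout.
3. **Allocation.** State what the block is and reconcile it with the three-slip envelopes. For participants not yet allocated, draw the order from a pre-generated list of the six sequences, blocked in sixes within each muscle-function group. Orders already used cannot be rebalanced, but the period term adjusts for them.

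The cost is revised analysis text and a new order list for the remaining participants. No extra visits or samples are needed.
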